#### 2.6.3. Withdrawal Criteria

Any participant who, after the beginning of this study, experiences events that may cause them to meet any of the exclusion criteria or to be in breach of the inclusion criteria shall be withdrawn from the trial. The data of the terminated subject will be collected until such time as non-compliance with the eligibility criteria is identified. No patients will be replaced, as the established sample size includes an additional 20% of participants to accommodate for potential losses.

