#### 2.6.1. Inclusion Criteria

Individuals over 65 years of age on the start date of this study.Individuals who are independent for activities of daily living or with mild functional dependence (Barthel Index score ≥ 60 and Short Physical Performance Battery (SPPB) ≥ 4).Independent for ambulation (can walk 45 m unaided or with a cane).Without cognitive impairment (Mini-Mental State Examination (MMSE) ≥ 24).With FOF (short FES-I ≥ 11).

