#### 2.6.2. Exclusion Criteria

People with the following medical diagnoses or health conditions (coded according to the International Classification of Diseases (ICD–10):-Diagnosis of mental, behavioral, or neurodevelopmental disorders: delirium, dementia, amnestic disorders, or other cognitive disorders (F05.0; F05.9; F00; F02.8; F03; F04; R41.3; F06.9). Mental disorders caused by a general medical condition, not elsewhere classified (F06.1; F07.0; F09). Schizophrenia or other psychotic disorders (F20; F22; F23; F24; F29).-Diagnosis of neurodegenerative diseases: Parkinson’s disease (G20); Alzheimer’s disease (G30); multiple sclerosis (G35); myasthenia gravis, or other myoneuronal disorders (G70).-Diagnosis of blindness or low vision (H54).-Diagnosis of conductive or sensorineural hearing loss, bilateral or uncorrected with a hearing aid (H90.0; H90.2; H90.5; H90.6; H90.8) or other types of hearing loss (H83.3; H91), as long as it impairs participants’ understanding.-Diagnosis of acute ischemic heart diseases and cerebrovascular diseases in the previous year (I20–I24; I60–I63; I67; I68).-Other diseases of the circulatory system that contraindicate the multicomponent physical exercise program [31]: other forms of heart disease (I30–I52) (e.g., uncontrolled atrial or ventricular arrhythmias, dissecting aortic aneurysm, severe aortic stenosis, acute endocarditis/pericarditis, uncontrolled arterial hypertension, acute thromboembolic disease, severe acute heart failure, severe acute respiratory failure, uncontrolled orthostatic hypotension; diabetes mellitus with acute decompensation or uncontrolled hypoglycemia (E10-E14), recent fracture in the last month (T14.2) (for strength training) or any other circumstance that the professional considers prevents this type of patients from performing physical activity in the program.Hospitalization during the recruitment period or expected admissions during the study period.Institutionalized patients or with frequent changes in address.

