### 4.4. Data Analysis

A descriptive analysis by groups (intervention and control) of participants’ sociodemographic, functional, and clinical characteristics will be carried out to identify potential differences between the two study groups, with quantitative variables expressed as either means and standard deviations or medians and interquartile ranges depending on the normality or skewness of data distribution. Qualitative variables will be summarized as frequencies and percentages. Data on the effect of the health education intervention will be analyzed in both the intention-to-treat population and the per-protocol population. In the former case, all participants will be included and will be analyzed as part of the group to which their PCF will be randomly assigned. Should the percentage of missing data be higher than 5%, multiple imputation techniques will be used. In the per-protocol analysis, complete cases of patients will be included provided they have maintained adherence. The intervention group is required to be adherent and have at least 80% attendance at the initial five sessions. Safety, acceptability, and feasibility of the health education intervention will also be assessed.

The primary efficacy analysis, (FOF), will be the comparison between intervention and control groups fitting a fixed-effects ANOVA model. Model will include group and facility as independent variables, with facility being a nested factor within group. The short FES-I scale mean scores and their 95% confidence intervals will be provided for each facility, or by groups if no differences between facilities are observed. The effectiveness of the health education intervention in relation to fear of falling will be measured through the decrease in the short FES-I scale scores, assessed at three times: at 1-, 6- and 12 months after the intervention. The difference in means between the intervention and control groups will be analyzed. In addition, the variable will be examined dichotomously, using a cut-off point on the short FES-I scale of 11 or more to identify the presence of fear of falling. Multivariate models will be fitted to identify factors potentially related to FOF.

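### As worded, the withdrawal rule ends follow-up for participants whose short FES-I falls below 11, so later observation of the primary outcome depends on the outcome itself

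*Protocol article*

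**What the plan says.** Under section 2.6.3, a participant whose situation changes after entry so as "to meet any of the exclusion criteria or to be in breach of the inclusion criteria shall be withdrawn from the trial". Information on that person "will be collected until such time as non-compliance with the eligibility criteria is identified". Withdrawn participants are not replaced; the section relies on the 20% allowance instead.

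The inclusion criteria in section 2.6.1 contain "With FOF (short FES-I ≥ 11" and "Independent for ambulation (can walk 45 m unaided or with a cane", as well as Barthel and SPPB minima. The exclusion criteria in section 2.6.2 contain "recent fracture in the last month (T14.2) (for strength training" and "Hospitalization during the recruitment period or expected admissions during the study period".

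Short FES-I is the primary outcome (section 2.11.1), measured at baseline and at 1, 6 and 12 months (Table 2). Section 2.2 places the hypothesis at 6 and 12 months. Section 4.4 promises an intention-to-treat analysis in which "all participants will be included and will be analyzed as part of the group" of their facility. It adds a dichotomous analysis of FES-I at 11, multiple imputation if more than 5% of data are missing, and a per-protocol analysis of complete cases. Section 4.2 repeats that participants leave only through the withdrawal criteria or by their own wish. Section 4.6 applies withdrawal during follow-up as well, and links it to a change in clinical condition and to safety.

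**The concern.** The entry threshold, the primary outcome and the cut-off of the dichotomous analysis are the same score on the same scale. A rule that withdraws people for no longer meeting entry criteria therefore withdraws those who respond. The favourable category of the dichotomous outcome is itself a withdrawal trigger.

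If the intervention works, more people cross the threshold in the intervention arm, so the loss differs by arm and selects the better outcomes. It falls on the 6- and 12-month visits, the times named in the hypothesis. Whether responders relapse by 12 months, a stated reason for the long follow-up, could not be observed. These participants' later falls would go unrecorded too.

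The falls outcome has its own route. A fall can cause a fracture, loss of independent walking or a functional decline, and each of these can end follow-up.

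**Working it through.** **1. The plan's own sample size.** Inputs from section 2.7: difference 3.8, SD 5.1, alpha 0.05 (taken as two-sided), power 80%, ICC 0.1, five facilities per arm.

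- Individual n per arm = 2 × [5.1 × (1.960 + 0.842) / 3.8]² = 28.28.
- Design effect at 12 per facility = 1 + 11 × 0.1 = 2.1.
- 28.28 × 2.1 = 59.4, so 60 per arm, 5 × 12, 120 in total.
- 120 / (1 − 0.20) = 150.

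The stated figures reproduce under the normal approximation. The point does not rest on an error in them.

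**2. What the rule removes, visit by visit (fear route).** Data are kept until non-compliance is identified, so the score that first falls below 11 is probably recorded.

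- 1 month: no loss.
- 6 months: missing if FES-I was below 11 at 1 month.
- 12 months: missing if FES-I was below 11 at 1 or 6 months.

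**3. Illustration.** From the documents: SD 5.1, effect 3.8, range 7 to 28, entry at 11 or more. Assumed: a normal source population with mean 15, and a common within-person correlation of 0.6. Four-visit profiles were simulated, rounded and limited to the scale range, and kept if baseline was at least 11. The intervention arm was shifted by 3.8 at follow-up, and the rule in step 2 was applied.

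| | Intervention | Control |
|---|---|---|
| No 6-month data | 36% | 12% |
| No 12-month data | about 51% | 20% |

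The 12-month difference is 3.5 with full data (below 3.8 because of the scale floor) and 2.4 among those still observed. Of 75 enrolled per arm, 75 × (1 − 0.51) ≈ 37 intervention and 75 × (1 − 0.20) = 60 control participants would remain at 12 months, before any ordinary dropout.

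**4. Sensitivity.** Over source means 13 to 17 and correlations 0.5 to 0.77 (the upper end is the test-retest ICC in section 2.11.1), missing 12-month data is 33–68% in the intervention arm and 9–34% in the control arm. The complete-case difference is about 2.0 to 2.8.

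A second construction, without truncation at entry and with control follow-up means of 13 to 19, gives 12-month losses of 25–76% (intervention) and 7–46% (control). In both constructions the loss is heavier in the intervention arm in every scenario, and its 12-month loss is above the 20% allowance.

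**5. Imputation.** Arm-specific regression imputation on the earlier scores, in the step 3 scenario, returns about 3.6 against 3.5 with full data. Over means 13–17 and correlations 0.5–0.7 it stays within about 0.1 of full data. The simulated data are nearly linear by construction, which favours this result.

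**6. Falls route.** No size was computed, because the documents give no rate of injurious falls. The reasoning is textual: recent fracture is an exclusion criterion, and independent walking and the Barthel and SPPB minima are inclusion criteria.

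**The case against.** **Intent.** Section 2.6.3 speaks of events, and section 4.6 ties withdrawal to clinical change and safety. Table 2 schedules FES-I for everyone to 12 months. A reader might infer that sites will in practice withdraw responders; the documents do not establish that. What stands against the objection is that section 2.6.3 covers the inclusion criteria without limit, and ten facilities may apply it differently.

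**Imputation.** A reader might infer that multiple imputation cannot repair the loss, or that 2.4 is what the primary analysis would report. Neither is supported. On the fear route, missingness depends on a recorded score, and step 5 shows good recovery of the mean difference. The figure of 2.4 is a complete-case result, not the planned intention-to-treat analysis. What remains is that nobody who earlier scored below 11 is ever observed later, so the imputed values are extrapolated from people who stayed at or above 11. The trial's own data could not test that model.

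**Intention-to-treat.** Analysis by assigned arm with imputation can coexist with withdrawals. The conflict is that the plan promises to include everyone while ending collection for a group defined by the outcome.

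**Admissions.** A reader might infer that any admission after a fall triggers withdrawal. Section 2.6.2 names only "Hospitalization during the recruitment period or expected admissions during the study period"; an unplanned admission alone is not clearly covered. It could count through fracture, lost function or the professional's discretion.

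**Fracture and function.** The fracture criterion carries a strength-training qualifier, and Table 2 schedules functional measures only at baseline and six months. The fall behind a fracture can be recorded before withdrawal. If falls are analysed as any fall to date, that person already counts as an event; the loss matters if each interval is analysed separately. This limb stands as a possibility of unknown size.

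**Conclusion.** The point holds on the text as written. Section 2.6.3 makes later observation of FES-I depend on FES-I, and it must be reconciled with sections 2.2 and 4.4 and Table 2. On the fear route the 1-month comparison is probably intact; the 6- and 12-month comparisons are affected.

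The sizes in the working are illustrative. They assume that the rule is applied literally, that the true effect is 3.8, and a source mean and correlation that the documents do not give. The direction (heavier loss in the intervention arm and a smaller complete-case difference) did not change over the ranges tried. The per-protocol analysis takes this selection in full. The intention-to-treat analysis may be close to right for the mean, but only through an assumption that cannot be checked.

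**What to change.** State in section 2.6.3 that short FES-I of at least 11 applies at enrolment only, and that a later score below 11 is an outcome and not a withdrawal event.

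Separate stopping the sessions from leaving outcome follow-up. Keep collecting FES-I and falls to 12 months unless consent is withdrawn, and analyse participants as randomised.

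Reconcile sections 2.6.3, 4.2, 4.4 and 4.6 with this. The clinical rules on who may take part in exercise should stay as they are; the change concerns data collection only, and the amended text must not loosen the existing safety rules.

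The cost is a short amendment, and follow-up visits that are already planned for these participants.

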### 2.7. Sample Size

We expect to be able to recruit ten PCFs (five assigned to the intervention group and five to the control group). Assuming a significance level of 0.05, a difference of 3.8 points on the Short Falls Efficacy Scale-International (FES-I), a standard deviation of 5.1 points, and an intraclass correlation coefficient of 0.1, at least 12 participants will be required per center (a total of 120 participants) to reach a power of 80%. Allowing for a loss of 20%, the necessary sample size will be 150 individuals (75 patients assigned to the intervention group and 75 to the control group; approximately 15 patients in each PCF, about five patients per nurse).

Patients seen by nurses at each participating facility and meeting the eligibility criteria will be recruited using a consecutive sampling method until the required sample size—which will be the same for all participating facilities—has been reached.

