### 2.8. Randomization

Ten PCFs will be randomly assigned to the intervention or control group, resulting in five facilities per arm. An allocation ratio of 1:1 will be used. The randomization will be performed using a random number generator. The study coordinator will run the generator and place the allocations into sealed envelopes.

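### Section 2.7 states 80% power, but ten randomised facilities leave 8 degrees of freedom, and on the plan's own inputs an unadjusted two-sided test has about 70%

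*Protocol article*

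**What the plan says.** Section 2.7 (Sample Size) works from four inputs: a 5% level, a target effect of 3.8 on the short FES-I, an SD of 5.1 and an ICC of 0.1. Its conclusion is that "at least 12 participants will be required per center (a total of 120 participants) to reach a power of 80" per cent. A 20% loss allowance then raises 120 to 150, about 15 per facility.

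Section 2.8 (Randomization) fixes the number of randomised units: "Ten PCFs will be randomly assigned to the intervention or control group, resulting in five facilities per arm".

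Section 4.4 (Data Analysis) plans a fixed-effects ANOVA for the primary outcome, with group and with facility nested in group. It lists no baseline term, and it does not say which variation the group effect is tested against.

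Section 2.7 names no formula, does not say whether the test is one- or two-sided, and mentions no correction for the small number of clusters.

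**The concern.** Facilities are randomised, and an ICC of 0.1 asserts that facilities differ. The group effect must therefore be judged against variation between facilities, which only ten facilities can estimate: 2 × (5 − 1) = 8 degrees of freedom. The design effect widens the standard error for clustering, but it does not allow for estimating that variation from so few units. Using 1.96 where 2.306 is needed overstates power.

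What is at stake is the stated risk of missing a true 3.8-point effect, the size named in the research hypothesis (section 2.2). That risk would be about 30%, not 20%. No estimate is biased by this.

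**Working it through.** **Inputs.** From section 2.7: α = 0.05, difference 3.8, SD 5.1, ICC 0.1, k = 5 facilities per arm, m = 12 analysed per facility (15 enrolled). Two-sided testing is assumed, because it reproduces the stated 12 and because section 4.4 reports 95% confidence intervals.

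**1. Reproducing the plan's figure.**
- Individually randomised n per arm = 2 × (1.960 + 0.842)² × (5.1/3.8)² = 28.28.
- With k fixed, m = 28.28 × (1 − 0.1) / (5 − 28.28 × 0.1) = 11.7, rounded up to 12.
- Check: the design effect is 1 + 11 × 0.1 = 2.1, and 28.28 × 2.1 = 59.4, so 60 per arm.
- Normal-approximation power is 80.4% at m = 12 and 78.9% at m = 11, so 12 is exactly the minimum.
- 120 / (1 − 0.2) = 150.

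One-sided readings do not give 12 as the minimum. One-sided z reaches 80% at m = 8 (81.9%), and one-sided t on 8 df reaches it at m = 11 (80.9%).

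**2. The same inputs on 8 degrees of freedom.** SE = 5.1 × √(2 × design effect / (5m)); noncentrality = 3.8 / SE; critical value t(0.975, 8) = 2.306.

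| Analysed per facility | Design effect | SE | Noncentrality | Power, z | Power, t on 8 df | Detectable at 80% |
|---|---|---|---|---|---|---|
| 12 | 2.1 | 1.349 | 2.816 | 80.4% | 69.5% | 4.32 |
| 15 | 2.4 | 1.290 | 2.945 | 83.8% | 73.3% | 4.13 |

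A simulation of 200,000 trials, using a t-test on facility means at m = 12, gives 69.7%. With ten facilities and no adjustment, 80% needs 26 analysed per facility. At 12 per facility, six facilities per arm give 79.4% and seven give 86.4%.

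**3. Whether the model in 4.4 changes this.** There are two ways to test group.
- Against facility-within-group: this is the 8 df test in step 2.
- Against the within-facility residual: per unit of total variance, the true variance of a facility mean is 0.1 + 0.9/12 = 0.175, but the test uses 0.9/12 = 0.075. The ratio is 2.333. The nominal cut-off of 1.98 (110 df) becomes 1.98/√2.333 = 1.30 true standard errors, so type I error is about 20%. The rejection rate at 3.8 points is about 94%, but that is not the power of a valid 5% test.

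**4. What baseline adjustment could recover (m = 12).** The baseline-to-follow-up correlation r is not in the document. The values below are assumptions.

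| What baseline explains | r = 0.3 | r = 0.5 |
|---|---|---|
| Within-facility variance only, 8 df | 71.2% | 74.3% |
| Both components, 1 df lost (7 df) | 71.7% | 79.6% |
| Both components, 8 df | 73.5% | 81.2% |

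For r = 0.5 on 8 df, the SE is 1.349 × √0.75 = 1.169 if both components fall. If only the within-facility part falls, it is 5.1 × √(0.4 × (0.1 + 0.9 × 0.75/12)) = 1.275.

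**The case against.** The strongest reply is that the plan's calculation is correct by its own method. The 12 and the 150 both reproduce, and the formula has to be inferred because none is named. That stands: there is no slip in the arithmetic. What is wrong is the use of a large-sample reference distribution for ten randomised units, and the power printed as a result.

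Second, 69.5% need not be the power of whatever test 4.4 leads to. That also stands, because 4.4 leaves the error term open. It does not rescue the 80%, since the alternative error term gives an invalid test (step 3). It does mean that 2.7 and 4.4 have to be corrected together.

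Third, sidedness is unstated, and a one-sided 5% test on 8 df would have 82.2% power at m = 12. That reading does not yield 12 as the minimum and sits poorly with the planned 95% intervals.

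Fourth, the shortfall depends on the ICC. At 0.05, power on 8 df is about 82%. But 0.1 is the value the plan chose.

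A reader might infer that adding baseline short FES-I restores 80% with no extra patients. The document does not support this. It gives no correlation. The 81% figure needs r = 0.5, baseline explaining facility differences as well as it explains patient differences, and no degree of freedom lost. Section 4.4 also measures effectiveness by the decrease in score, so 5.1 may already be the SD of change, in which case the 1 − r² factor does not apply. A reader might also infer that a null result will be taken as evidence against a 3.8-point effect. Nothing in the document says so, and confidence intervals are planned.

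**Conclusion.** Wrong as written. With five facilities per arm, ICC 0.1, SD 5.1 and a two-sided 5% level, a valid unadjusted comparison has about 70% power for 3.8 points with 12 analysed per facility. Even with no losses it has about 73%. The difference detectable with 80% power is about 4.3 or 4.1 points. These figures assume equal cluster sizes and two-sided testing; that the plan used a normal approximation is inferred from the exact match at 12.

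A statistical analysis plan that is not shown could specify the test, but it could not make the power printed in 2.7 true for an unadjusted comparison on these inputs. How much power baseline adjustment would recover cannot be settled from the document.

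**What to change.** 1. In 2.7, state the formula and sidedness, and restate power on the t distribution with 8 df: about 70% for 3.8 points with 12 analysed per facility and 73% with 15, with detectable differences of about 4.3 and 4.1 points.
2. In 4.4, state that group is tested against facility-within-group variation. Without this, the sample size and the analysis do not match.
3. Optionally, add the baseline short FES-I, already collected, to the primary model. If so, state whether 5.1 is the SD of a follow-up score or of change, the correlation assumed, which variance components it is expected to reduce and the degrees of freedom used, and give power as a range (at r = 0.5 and 12 per facility, 74% to 81%). Do not state that 80% is restored without these assumptions.

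The cost is revised text and a less favourable power figure. Items 1 and 2 need no new data and no change to recruitment. If the sponsor wants 80% without relying on baseline adjustment, more facilities or more patients per facility would be needed, as step 2 of the working shows.

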### 2.8. Randomization

Ten PCFs will be randomly assigned to the intervention or control group, resulting in five facilities per arm. An allocation ratio of 1:1 will be used. The randomization will be performed using a random number generator. The study coordinator will run the generator and place the allocations into sealed envelopes.

### 2.9. Study Blinding

The intervention can only be blinded during participant recruitment, when the professionals in the Clinical Care Group will not know to which group they will be assigned. To avoid interpretation bias throughout the statistical analysis, patient information will be encoded. The data analysis will be performed by a third party not involved in the fieldwork. The principal investigator will assess the results and participate in the fieldwork at one PCF, which means that she cannot be blinded when assessing the results obtained.

